**Figure 1 F1:**
[figure not shown]
Study protocol of the Enhancing Safety in Epilepsy Surgery (EASINESS) registry.

### Data Management

Data collection will be performed locally at each site and de-identified in an independent database, then submitted to the Department of Neurosurgery at University Medical Center Hamburg-Eppendorf (Germany). All results, including patient-specific data, surgical techniques, complications, and long-term outcomes, will be submitted for publication in peer-reviewed journals and/or reported at professional scientific meetings. Every participating center can submit further scientific questions which will be evaluated by the steering committee for approval or rejection. The by-laws of the steering committee are accessible from the principal investigator upon request. This study is indexed at clinicaltrials.gov (NT 04952298).

### Statistics

The endpoints will be evaluated using descriptive statistics, and the key figures of the distributions will be presented in tables. Statistical analyses will be made as described in previous studies which established the concept of benchmarking for other surgical procedures (10, 11, 15). Hereby, the cohort is stratified into patients with a low-preoperative and high-preoperative risk profile according to comorbidities which are proven to negatively impact the postoperative course. Afterward, the benchmark cut-off for each outcome indicator is set at the 75th percentile of the median of all centers (10). Depending on the composition of the data, χ2, Mann-Whitney U, and *t*-tests, or Pearson or Spearman correlation coefficients, will be conducted. The relationships between multiple independent variables on the dependent variable(s) will be tested using multivariate regression analysis.

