## Abstract

**Introduction:** Optimizing patient safety and quality improvement is increasingly important in surgery. Benchmarks and clinical quality registries are being developed to assess the best achievable results for several surgical procedures and reduce unwarranted variation between different centers. However, there is no clinical database from international centers for establishing standardized reference values of patients undergoing surgery for mesial temporal lobe epilepsy.

**Design:** The Enhancing Safety in Epilepsy Surgery (EASINESS) study is a retrospectively conducted, multicenter, open registry. All patients undergoing mesial temporal lobe epilepsy surgery in participating centers between January 2015 and December 2019 are included in this study. The patient characteristics, preoperative diagnostic tools, surgical data, postoperative complications, and long-term seizure outcomes are recorded.

**Outcomes:** The collected data will be used for establishing standardized reference values (“benchmarks”) for this type of surgical procedure. The primary endpoints include seizure outcomes according to the International League Against Epilepsy (ILAE) classification and defined postoperative complications.

**Discussion:** The EASINESS will define robust and standardized outcome references after amygdalohippocampectomy for temporal lobe epilepsy. After the successful definition of benchmarks from an international cohort of renowned centers, these data will serve as reference values for the evaluation of novel surgical techniques and comparisons among centers for future clinical trials.

**Clinical trial registration:** This study is indexed at clinicaltrials.gov (NT 04952298).

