## Materials and Methods

### Study Design

The EASINESS is a retrospectively conducted, multicenter, open registry. The study is a procedure-specific registry, initiated by the Department of Neurosurgery, University Medical Center Hamburg-Eppendorf, Germany. The selected members of participating neurosurgical or epilepsy centers will be invited to form a Steering Committee, which will be responsible for the scientific goals and guarantee the reliability of the data analysis. Neurosurgical, neurological, and epilepsy units from all countries are invited to join the trial and to recruit patients if the center- and patient-specific inclusion criteria are met.

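### The association analyses name tests that assume independent patients and state no allowance for centre, so inference on factors that follow centre practice would be anti-conservative

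*Protocol article*

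**What the plan says.** The Study Design section sets the structure of the data: "The EASINESS is a retrospectively conducted, multicenter, open registry". The Abstract gives part of the motivation for benchmarks and registries as the wish to "reduce unwarranted variation between different centers".

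The Statistics section describes two kinds of analysis.

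- **Descriptive benchmarking.** "The endpoints will be evaluated using descriptive statistics, and the key figures of the distributions will be presented in tables". For the benchmark itself, "the benchmark cut-off for each outcome indicator is set at the 75th percentile of the median of all centers (10"). The unit here is the centre.
- **Association analyses.** The list opens with "Depending on the composition of the data, χ2, Mann-Whitney U, and" t-tests and continues "or Pearson or Spearman correlation coefficients, will be conducted". The next sentence is "The relationships between multiple independent variables on the dependent variable(s) will be tested using multivariate regression analysis". No unit of analysis is given for the tests or the regression. No centre term, random effect, robust standard error or stratification by centre is mentioned, and none is excluded.

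The section also refers to earlier benchmarking studies for its methods; these are not available here.

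**The concern.** The data are patients within centres. In standard form each listed test and correlation treats its observations as independent, and the stated basis for choosing among them is the make-up of the data, not the nested design. The article does not say outright that the tests are applied to pooled patients, but that is the natural reading. The Case Report Form section describes variables recorded for each patient, and only the benchmark sentence moves to centre-level summaries.

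If patients from one centre resemble each other in outcome, and a factor such as procedure type, navigation or operating duration also follows local practice, two things go wrong.

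- **Precision.** One centre's habit is counted as many independent observations. Standard errors are too small, p-values too small and intervals too narrow.
- **Confounding.** The factor is mixed up with everything else that distinguishes the centre, so an apparent technique effect may be a centre effect.

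This matters because the Introduction and Discussion intend the data to serve as a reference for evaluating new surgical techniques and for comparing centres. A reported link between technique and outcome is a result that readers would be likely to use.

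**Working it through.** **There is no plan figure to reproduce.** The article gives no sample size, number of centres, patients per centre, ICC or significance level. The figures below show the possible size under stated assumptions.

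**Inputs**

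- Cluster size m (patients per centre): assumed. The Center-Specific Inclusion Criteria require an average of 30 or more seizure-specific resections per year over five years, so 30 × 5 = 150 or more per centre under the standard criterion. The mesial temporal share is not given, and some international centres may enter under local guidelines. I use m = 60 as the main case and 30 to 150 as the range.
- ICC of the outcome (ICC_y): assumed, 0.01 to 0.05 in the main case and up to 0.10 in the range.
- ICC of the factor (ICC_x): 1 if constant within centre; 0.05 or 0.20 if partly centre-driven. Assumed.
- Nominal two-sided level: 5%, assumed.

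**Formulas**

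- Design effect, factor constant within centre: DE = 1 + (m − 1) × ICC_y
- Design effect, factor partly centre-driven: DE = 1 + (m − 1) × ICC_y × ICC_x
- True error of the naive test: 2 × (1 − Φ(1.96 / √DE))

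**Factor constant within centre, m = 60**

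| ICC_y | DE | True error |
|---|---|---|
| 0.01 | 1 + 59 × 0.01 = 1.59 | 12.0% |
| 0.02 | 1 + 59 × 0.02 = 2.18 | 18.4% |
| 0.05 | 1 + 59 × 0.05 = 3.95 | 32.4% |

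A naive 95% interval would then cover about 88%, 82% and 68% (100% minus the true error). With m = 90 and ICC_y = 0.05, DE = 1 + 89 × 0.05 = 5.45 and the error is about 40%. Over m = 30 to 150 and ICC_y = 0.01 to 0.10, DE runs from 1.29 to 15.9 and the error from about 8% to 62%.

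**Factor partly centre-driven, m = 75, ICC_y = 0.05**

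| ICC_x | DE | True error |
|---|---|---|
| 0.05 | 1 + 74 × 0.05 × 0.05 = 1.185 | 7.2% |
| 0.20 | 1 + 74 × 0.05 × 0.20 = 1.74 | 13.7% |

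**Simulation check.** An ordinary chi-squared test was run under a true null with beta-binomial centre rates: 20 centres of 50 patients, event rate 0.65, 4,000 runs per setting (all assumed).

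| ICC_y | Factor constant within centre | Factor balanced within centres |
|---|---|---|
| 0.02 | 17% | 4.5% |
| 0.05 | 30% | 3.9% |
| 0.10 | 42% | 3.8% |

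For m = 50 and ICC_y = 0.05 the formula gives DE = 1 + 49 × 0.05 = 3.45 and an error of 29%, in line with the simulated 30%. For a factor balanced within centres the test is slightly conservative.

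**The case against.** The strongest reply is that this is a condensed article. Model form, unit of analysis and the handling of centre are details that such an article may leave to a full protocol or SAP, and neither is shown. A reader might infer from the regression sentence that centre will be ignored. The text does not support that: a model with a centre term or random effect fits the sentence equally well, and the cited benchmarking studies may or may not deal with centre. This part of the objection stands, and the regression sentence alone would not carry the point. What carries it is the explicit list of tests and correlations, which in standard form have no place for centre. An analysis plan that handled clustering properly would have to replace them or reduce them to description.

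A second reply is that the main output is untouched. This also stands. The endpoints are evaluated descriptively and the cut-off is a percentile of centre medians, so the centre is already the unit and no p-value is attached.

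Third, a reader might fear that inflated p-values would feed into the low-risk and high-risk groups. The Statistics section bases these groups on comorbidities whose adverse effect it treats as already established. Nothing says that they will be derived from tests in the registry.

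Fourth, the larger error rates are a worst case. They apply to a factor constant within centre, and the documents do not show that any recorded variable is of that kind. The inflation should not be carried over to factors such as age or sex if these are roughly balanced across centres.

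**Conclusion.** The point holds for the secondary association analyses. Applied to pooled patients, the named tests and correlations are anti-conservative for factors that follow centre practice, and the associations they yield may be centre effects. The size depends on the factor:

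- constant within centre: true error about 12% to 32% at a nominal 5% (m = 60, ICC 0.01 to 0.05);
- partly centre-driven: about 7% to 14% (m = 75, outcome ICC 0.05, factor ICC 0.05 to 0.20);
- balanced within centres: no inflation.

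These figures rest on assumed cluster sizes and ICCs. That procedure type, navigation or operating duration follow centre practice is also an assumption, though a plausible one. The conclusion does not extend to the benchmark cut-offs or to the risk stratification, and it is not a finding that the regression leaves centre out. The change should be made, because the multicentre design and the study's interest in differences between centres make independence hard to defend.

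**What to change.** In the statistical section, or in the SAP if one exists:

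1. State the unit of analysis for each test and for the regression.
2. For inferential patient-level associations, use regression that accounts for centre: a random centre intercept (logistic for binary outcomes, proportional odds for ILAE class, linear for continuous outcomes), or GEE or cluster-robust standard errors with centre as cluster. Because the number of centres is not given, specify a small-sample correction for GEE or robust errors if centres turn out to be few.
3. For practice variables such as procedure type, navigation and operating duration, estimate within-centre and between-centre effects separately, for example by entering the centre mean and the patient's deviation from it. A random intercept alone does not separate the two.
4. Keep the chi-squared, Mann-Whitney U and t-tests and the correlations as descriptive only.

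No new data are needed, since centre must already be identifiable to compute centre medians. The cost is a few sentences, a little more analysis work with standard software, and somewhat wider intervals. The benchmark calculation stays as it is.

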### Registry Reports

The results of the EASINESS registry will be published by the Steering Committee and distributed to all participating centers following careful analysis by the principal investigators ([name] and [name]) at the Department of Neurosurgery, University Medical Center Hamburg-Eppendorf.

## Discussion

In recent years, quality monitoring and improvement have become more important in the field of healthcare, especially in surgery (20, 21). As a various single- and multiple-outcome indicators for evaluating the quality of surgical procedures were introduced, the concept of benchmarking as introduced by Staiger et al. seems to be the most reliable concept for establishing standardized outcome references and defining acceptable outcomes (10). Benchmarking offers an opportunity to present valid, internationally applicable reference values which originate from the daily routine of a large representative cohort. This will be the first internationally validated benchmark data for neurosurgery and as such will demonstrate that such data collection is both feasible and useful.

Unlike data from randomized controlled trials, which have stringent patient selection criteria and questionable generalizability, this study has only a few patient-specific inclusion criteria, and the results will therefore be generalizable to usual neurosurgical practice.

The EASINESS is a retrospectively conducted, multicenter, open registry with narrowly defined inclusion criteria for international centers. The objective is the application of the previously described benchmarking to define robust and standardized outcome references after temporal lobe epilepsy surgery. Afterward, these benchmarks from an international cohort of high-volume centers will serve as reference values for the evaluation of novel surgical techniques and comparisons among centers or future clinical trials. Furthermore, EASINESS has been established with an interdisciplinary approach collecting outcome data from both a neurosurgical and epileptogenic perspective and presenting novel valuable data compared with existing registries.

### Limitations of This Study

The results of this registry should be interpreted considering the limitation that the study design is a retrospective, non-randomized design which could introduce some bias.

## Ethics Statement

The studies involving human participants were reviewed and approved by Local Ethics Committee Hamburg 2021-300051-WF. Written informed consent to participate in this study was provided by the participants' legal guardian/next of kin.
